**Methods:**

A stepped wedge cluster randomized controlled trial will be conducted over 3 years across three Australian states. One hundred participants with dementia and/or their carers/family members will be randomly selected from community health center client lists in each state to receive either the dementia “*Support for Life*” intervention (Group A) or routine care (Group B). Group A participants will have access to the intervention from year 1. Group B participants will continue to receive usual care and will not be denied information on dementia or dementia services in year 1. In year 2, Group B participants will have access to the intervention. A highly trained expert dementia support worker will provide the “*Support for Life*” intervention, which is a flexible, individually tailored, holistic support that is relationship-centered, focused on enablement as opposed to dysfunction, and facilitate participants’ continued engagement in their community and the workforce. Additionally, dementia education, information resources, advocacy, and practical support to navigate and access dementia services and health care will be provided. The mode of support will include face to face, telephone, and internet interaction on an “as needed basis” for 12 months. The primary hypothesis is that the intervention will improve the quality of life of people with dementia and the health and well-being of carers/family through facilitating the continuation and enhancement of regular daily activities. Secondary hypotheses will examine other health and service usage outcomes. The outputs will also include a health economic analysis to investigate the costs (and savings) of any associated reduction in unnecessary health services use and delay in accessing permanent residential aged care.

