### Trial Design

The evaluation of the “*Support for Life*” complex intervention will occur within a step-wedge cluster Randomized Controlled Trial (cRCT) involving multiple community health centers across three states over 3 years. Clusters are the community health centers, and approximately 10 centers in each state will participate in this study. Half of the centers (Group A) will be randomized to receive the intervention in year 1 and the other half in year 2 (Group B).

This “*Support for Life*” complex intervention proposes to trial a framework of a single service, highly flexible holistic approach to support for people with dementia and their families/carers. It will provide a platform to integrate current services and health care, provide emotional support, and enhance community and social engagement. Important principles are
Protecting the person with dementia and their rights to full citizenship regardless of their age, gender, and cultural background.Providing access to support where there is diminished decision-making capacity, retaining respect for the person with dementia but also the advocating for the rights of the family and caring unit.Improving access to palliation and “end of life care” in the setting of advanced or impaired decision-making, including with those who live alone.

This type of response builds on the strengths in a caring unit and addresses the needs of individual relationships. In line with “codesign” and “consumer directed care” (CDC) principles, the person with dementia, their family, and other members of the caring unit will actively design/influence what this service response will look like. Ongoing evaluation will allow for flexibility and change.

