### Intervention

Dementia Support Workers, recruited from each of the three states, will inform the Community Health Centers of our trial of the provision of dementia friendly support to their patients by assisting them in getting the right services and the right people at the right place.

Group A participants will be from Group A cluster sites and will have access to the “*Support for Life*” intervention from year 1. This “*Support for Life*” complex intervention proposes to trial a framework of a single service, highly flexible holistic approach to support for people with dementia and their families/carers. It will provide a platform to integrate current services and health care, provide emotional support, and enhance community and social engagement by
Working with the “person with dementia or cognitive impairment and those who support them” regardless of age, gender, and cultural background.Focusing on strengths of the people involved in order to maintain and improve physical and emotional health and well-being.Planning for the future to provide peace of mind.Use of an assistant and volunteers to help identify/create/facilitate access to services and enhance the social engagement of people with dementia or their carers and families in response to their stated goals or needs.Recognizing the challenges for young people and children and actively prototyping within the setting of their situation. It will require age appropriate responses and support mechanisms.

Group B participants will continue to receive usual care by health service providers and will not be denied information on dementia or dementia services in year 1. In year 2, Group B participants will have access to the “*Support for Life*” intervention making this a step-wedge study design. In year 2, Group A participants, who receive the intervention in year 1, may still access the intervention, but the intervention will no longer be actively promoted at those sites. See Figure 1 for the trial design.

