#### Blinding (Masking)

The Research Officer undertaking the data collection will be blinded to participant group allocation. Participants (people living with dementia or cognitive impairment in the community, carers of people with dementia or cognitive impairment living in the community, and family members of people with dementia or cognitive impairment living in the community) will be blinded to their group allocation.

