## Methods: Data Collection, Management, and Analysis

Primary and secondary data collection will occur at baseline and 3, 6, 12, 15, 18, and 24 months post-randomization (Figure 1). This will involve a face to face visit with a researcher. Participants will receive a telephone call and an information letter with study questions 10 to 14 days prior to the baseline and all follow-up visits. The telephone contact will be used to arrange a mutually suitable time and location for the face to face visit as well as provide information to participants about what will take place at the forthcoming visit. Participants will have the option to complete questionnaires prior to the visit or complete them during the researchers visit. Interviews will take place during the face to face visit and will be audio-taped prior to transcription and importation into the NVivo Qualitative Software to aid analysis. The researcher will be trained in quantitative and qualitative data collection methods and any relevant outcome measure assessments. They will also be experienced in communicating with people with dementia and their carers and families including collecting data from participant and proxy (carer/family member) when necessary.

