## Ethics and Dissemination

The Support for Life study involves working with participants who are living with memory loss or dementia and their carers and families. To ensure that the needs of these participants are met, the research team includes investigators with expert knowledge in dementia and aged care services.

Approval to conduct the study has been applied for from the RDNS Human Research Ethics Committee in Victoria and will also be sought from The University of Sydney Human Research Ethics Committee in New South Wales and the Queensland University of Technology Human Research Ethics Committee in Queensland. All participants will be provided with detailed written information and have an opportunity to discuss participation before providing written or verbal consent. Verbal consent will be audio-taped. Participants will be advised that they can withdraw from the study at any point.

Any required modifications to the study protocol, such as changes to eligibility criteria, outcomes, and analyses, will be discussed by the study investigators and after agreement is reached will be submitted to the abovementioned Ethics committees for approval. Amendments describing any modifications to the study protocol will also be made to the relevant trials registry.

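### The protocol says participants, carers and family members are blinded, but the openly delivered programme rules this out, so post-baseline QOL-AD and CES come from unblinded reporters

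*Protocol article*

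**What the plan says.** The Blinding (Masking) section of the protocol article makes two statements. On the assessor: "The Research Officer undertaking the data collection will be blinded to participant group allocation". On people with dementia, carers and family members, all three listed: they "will be blinded to their group allocation". Neither statement is limited in time, and neither names a means of achieving the masking.

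Other sections describe what participants experience:

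- **Abstract, Methods:** "The mode of support will include face to face, telephone, and internet interaction on an" as-needed basis, for 12 months.
- **Trial Design:** "the person with dementia, their family, and other members of the caring unit will actively design/influence what this service response will look like".
- **Intervention, year 1 comparator:** "Group B participants will continue to receive usual care by health service providers". No sham or attention control is described.
- **Intervention, crossover:** "In year 2, Group B participants will have access to the" programme.
- **Schedule of Events:** the programme is promoted at the clusters that are in their intensive phase.

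The primary outcomes are QOL-AD for the person with dementia and CES for the carer or family. The data collection section lets participants fill in questionnaires before or during the researcher's visit, and provides for a carer or family proxy when necessary. It adds: "Interviews will take place during the face to face visit".

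**The concern.** A person who is visited and telephoned by a support worker, and who helps shape that support, knows that they are receiving it. A person on usual care, with access due in the following year, has no reason to believe that they are receiving it. The article therefore claims a protection that its own description of the trial excludes.

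The claim bears on both primary outcomes, because each is a subjective report by the person with dementia, the carer, or a family proxy who is also a target of the programme. Expectation, gratitude or disappointment could move the scores without any change in quality of life or caring experience. A reader who relies on the blinding statement would discount that explanation too readily. The Strengths and Limitations section does not mention unblinded reporting.

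**Working it through.** **1. Can participant blinding hold?** The article gives no stated figure on this point, so the sections are set side by side.

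| Feature | Section | Compatible with being unaware of allocation? |
|---|---|---|
| 12 months of contact with a support worker | Abstract, Methods | No |
| Recipients help design the service | Trial Design | No |
| Usual care, no sham or attention control | Intervention | No |
| Group B starts in year 2 | Intervention | No; the change is visible |
| Programme promoted at intensive-phase clusters | Schedule of Events | No |
| Randomization follows baseline assessment | Allocation Concealment Mechanism | Yes, for baseline scores only |

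Baseline scores precede allocation. Every later score is given with knowledge of the support received.

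**2. Does masking the Research Officer help?** The officer collects the answers, but the participant or proxy supplies them. Masking the collector protects against the collector's influence and not against the respondent's own expectation.

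**3. When is the officer's masking at risk?** There are six follow-ups: 3, 6, 12, 15, 18 and 24 months. Under Schedule of Events, months 3 and 15 carry only the primary measures. In Table 1, the RUD and the interview or client-record items on activities and engagement fall at 6, 12, 18 and 24 months, so four of the six follow-ups ask directly about services or activities. The groups differ most in exposure at 6 and 12 months. In year 2 both have access, so mention of support separates them less.

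**4. How sensitive is the result?** Inputs from Sample Size: effect sizes 0.23 (QOL-AD) and 0.25 (CES), SDs 7 and 10, power 0.80, significance level 0.05 (taken as two-sided; the article does not say), ICC 0.05, 30 clusters, seven time points.

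*Planned effect sizes.* A Hussey-Hughes model was used on cluster-period means, with Group A exposed from the second measurement and Group B from the fifth, and no separate within-person correlation. The detectable effect is (1.96 + 0.84) × SE:

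- 10 per cluster: 2.80 × 0.0798 = 0.224 SD
- 8 per cluster (20% attrition): 2.80 × 0.0881 = 0.247 SD

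This broadly agrees with the stated 0.23-0.25.

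*Targets in scale points.* 0.23 × 7 = 1.61 on QOL-AD; 0.25 × 10 = 2.5 on CES.

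*Chance of p<0.05 with no true effect and a reporting bias b.* Let SE = target/(1.96 + 0.84), that is 0.23/2.80 = 0.082 and 0.25/2.80 = 0.089. Then

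P = Φ(b/SE − 1.96) + Φ(−b/SE − 1.96).

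Example, QOL-AD with b = 0.10: b/SE = 1.22, so P = Φ(−0.74) + Φ(−3.18) ≈ 0.23.

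| Assumed bias (SD) | QOL-AD points | P, QOL-AD | CES points | P, CES |
|---|---|---|---|---|
| 0.05 | 0.35 | 9% | 0.5 | 9% |
| 0.10 | 0.70 | 23% | 1.0 | 20% |
| 0.15 | 1.05 | 45% | 1.5 | 39% |
| 0.20 | 1.40 | 68% | 2.0 | 61% |

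The bias values are assumptions; the article gives none. The formula also treats the bias as a constant shift in intervention periods relative to control periods.

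**The case against.** Blinding of participants is not feasible for a support-worker programme, so its absence is not a poor design choice, and any reader can see what the intervention is. That is right, and the point is narrower: the article affirms a property that the trial lacks and does not list the resulting limitation. This is a positive statement contradicted within the article, so condensation from a fuller protocol does not explain it.

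A charitable reading is that participants are masked to the group label or the hypothesis, or only until randomization. The text says allocation and sets no time limit, and the baseline period is covered separately under allocation concealment. This reading softens the point but does not remove it.

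Several stronger readings are tempting, and the documents do not support them:

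- **Both primary outcomes are purely self-rated.** The Outcomes section names no rater, the data collection section allows proxies, and Inter-Rater Reliability mentions researchers' ratings of quantitative data. Self- or proxy-reported is as far as the text goes.
- **The consent material reveals the group.** The article says "All participants will be provided with detailed written information", but that material is not shown, so what it discloses about the two groups is unknown. The conclusion does not need it.
- **The Research Officer is unmasked at every visit.** Months 3 and 15 carry only primary measures under Schedule of Events (the data collection section is looser on this), and questionnaires may be completed before the visit. The risk is real at the other four follow-ups, but it is not a certainty.
- **The bias has a known size.** A single value such as 0.1 SD, which is 0.1/0.23 = 43% or 0.1/0.25 = 40% of the targets, would only restate an assumption.

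**Conclusion.** The participant-blinding statement is wrong as written and should be corrected. The contradiction is internal and rests on no calculation. After baseline, QOL-AD and CES are reported by people who know what support they receive. Masking of the Research Officer is worthwhile, but it does not protect these reports and may itself be broken at 6, 12, 18 and 24 months.

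The size of any bias cannot be derived from the article. The ranges of roughly 9-68% for QOL-AD and 9-61% for CES are illustrative. They assume no true effect, a constant bias of 0.05 to 0.20 SD, a two-sided 5% test, and standard errors that give exactly 80% power at the stated targets. They show that, with targets this small, a modest bias could matter; they do not show that one will occur. A reader might infer that the trial is invalid or needs redesign. The documents do not support that: the trial stays viable, and the correction alters how its primary results may be described and interpreted.

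**What to change.** 1. **Blinding (Masking):** state that participants, carers, family members and support workers are not blinded, and that masking of the Research Officer is intended but may be broken.
2. **Order of forms:** have QOL-AD and CES completed before the visit, which is already allowed, or first at the visit, ahead of the RUD and interviews.
3. **Record of unmasking:** at each visit, note whether the officer learned the group.
4. **Limitations and reporting:** list unblinded self- or proxy-report as a limitation. Read the primary results beside the data already planned on entry to residential care and administrative service use. These are less subjective but not immune, since families and support workers who know the allocation can influence them.

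A general request that participants not mention their support is better left out, because the RUD and interviews ask about service use. If used, it should apply only until the primary questionnaires are complete.

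The cost is a change of wording, a fixed order of forms and one tick-box per visit. The reported blinding status becomes less favourable. The design, sample size and analysis model are unchanged.

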## Methods: Data Collection, Management, and Analysis

Primary and secondary data collection will occur at baseline and 3, 6, 12, 15, 18, and 24 months post-randomization (Figure 1). This will involve a face to face visit with a researcher. Participants will receive a telephone call and an information letter with study questions 10 to 14 days prior to the baseline and all follow-up visits. The telephone contact will be used to arrange a mutually suitable time and location for the face to face visit as well as provide information to participants about what will take place at the forthcoming visit. Participants will have the option to complete questionnaires prior to the visit or complete them during the researchers visit. Interviews will take place during the face to face visit and will be audio-taped prior to transcription and importation into the NVivo Qualitative Software to aid analysis. The researcher will be trained in quantitative and qualitative data collection methods and any relevant outcome measure assessments. They will also be experienced in communicating with people with dementia and their carers and families including collecting data from participant and proxy (carer/family member) when necessary.

### Inter-Rater Reliability

To ensure consistency of the interpretation/coding of the qualitative interview data and the measurement of the quantitative data, we will calculate the correlation between the ratings of two researchers. Data coded into the statistical software will also be checked to ensure its accuracy.

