### Sample Size

The study is powered to detect small–medium effects in the primary outcome measures of QOL-AD for people with dementia or cognitive impairment (0.23 effect size) and in the CES for carers (0.25 effect size).

The sample size required is 30 clusters with 10 participants/families in each to allow for an attrition of 20%. This is a total of 100 participant/families (50 in each group) in each of the 3 states, making a total sample size of 300. This will detect significant differences in caregiver’s and people with dementia or cognitive impairment’s quality of life between two groups at effect sizes of 0.23–0.25 (small–medium effects). Sample size calculations were completed using STATA statistical software stepped wedge: for clusters defined at the level of the community health center, power of 0.80, significance level set at 0.05, intraclass correlation coefficient (ICC) of 0.05, the number of steps (2), participant data collected at seven time points (baseline, 3, 6, 12, 15, 18, and 24 months), and primary outcome distributions as described in existing literature, i.e., QOL-AD scores between 15 and 60 and SD of 7 (6, 7, 14, 15) and CES scores between 0 and 100 and SD of 10 (8, 9).

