#### Qualitative Analysis

Interview transcripts and journal entries will be managed using QSR NVivo (Qualitative Solutions and Research, Melbourne, Victoria). Interview data will be initially coded into broad topic areas using content analysis, and then constant comparative method will be applied to develop theoretical insights.

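### Rater consistency is to be checked by a correlation, which misses a systematic difference between raters and has no meaning for interview data coded into topic categories

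*Protocol article*

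**What the plan says.** The Inter-Rater Reliability section gives its aim as "To ensure consistency of the interpretation/coding of the qualitative interview data and the measurement of the quantitative data". For that aim it names one statistic: "we will calculate the correlation between the ratings of two researchers". The type of correlation is not stated, and no agreement measure is named there or elsewhere in the article.

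The section's other sentence, "Data coded into the statistical software will also be checked to ensure its accuracy", concerns data entry. It does not compare raters. Nor do the error screening under Data Management or the researcher training described under Methods: Data Collection, Management, and Analysis.

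The kind of data to be coded is clear from Qualitative Analysis: "Interview data will be initially coded into broad topic areas using content analysis". Topic areas are categories without a natural order.

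**The concern.** Consistency between two raters means that they give the same answer for the same participant or transcript. A correlation asks a weaker question, namely whether one rater's values rise and fall linearly with the other's. Two gaps follow.

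- **Quantitative scores.** If one researcher records every score a fixed amount higher than the other, the correlation is the same as if they agreed.
- **Interview codes.** A correlation needs numbers. Numbers attached to topic areas are arbitrary labels, so the coefficient reflects the labelling as well as the coders' behaviour.

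What is at stake is whether the reliability statement can be believed. Table 1 lists interviews or client records as the source for several secondary outcomes: social activities, social engagement and access to residential care for the person with dementia, and social engagement for carers. The article does not say how interview material becomes those variables, so no effect on a particular result can be sized.

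**Working it through.** The article gives no reliability coefficient, threshold or number of double ratings, so there is no planned figure to reproduce. The check is an illustration on the plan's own scales.

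**Inputs from the Sample Size section.** "QOL-AD scores between 15 and 60 and SD of 7" and "CES scores between 0 and 100 and SD of 10", with target effects of 0.23 SD for QOL-AD (0.23 × 7 = 1.61 points) and 0.25 SD for CES (0.25 × 10 = 2.5 points).

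**Assumptions, not in the document.** A between-rater correlation r of 0.95 or 0.90, equal SDs for the two raters, a constant offset d, and the code frequencies and confusion pattern in step 3.

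**Step 1: the correlation.** Adding a constant d to one rater's scores changes neither the covariance nor the SDs, so r is unchanged for every d. This needs no assumption about r.

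**Step 2: absolute agreement.** For two raters with equal SD and offset d, the single-rating absolute-agreement ICC is r·SD² / (SD² + d²/2).

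| Scale | r | Offset d | Calculation | ICC |
|---|---|---|---|---|
| QOL-AD | 0.95 | 1.61 | 46.55 / (49 + 1.30) | 0.93 |
| QOL-AD | 0.95 | 3 | 46.55 / (49 + 4.5) | 0.87 |
| QOL-AD | 0.95 | 5 | 46.55 / (49 + 12.5) | 0.76 |
| QOL-AD | 0.90 | 1.61 | 44.1 / (49 + 1.30) | 0.88 |
| QOL-AD | 0.90 | 3.5 | 44.1 / (49 + 6.125) | 0.80 |
| QOL-AD | 0.90 | 7 | 44.1 / (49 + 24.5) | 0.60 |
| CES | 0.90 | 2.5 | 90 / (100 + 3.125) | 0.87 |
| CES | 0.90 | 5 | 90 / (100 + 12.5) | 0.80 |
| CES | 0.90 | 10 | 90 / (100 + 50) | 0.60 |

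In every row the correlation stays at the value in the second column. A simulation of 200,000 rating pairs at r = 0.90 gave the same ICCs.

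At an offset equal to the QOL-AD target effect, the ICC falls only from 0.95 to 0.93. An ICC alone would hardly flag it. The mean difference, 1.61 points, shows it directly.

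**Step 3: nominal codes.** Assume four topic codes A, B, C, D with frequencies 0.4, 0.3, 0.2, 0.1 for coder 1. Coder 2 swaps A and D 30% of the time and otherwise agrees.

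- Agreement: 1 − 0.3 × (0.4 + 0.1) = 0.85.
- Coder 2's frequencies: A 0.31, B 0.30, C 0.20, D 0.19.
- Chance agreement: 0.4 × 0.31 + 0.3 × 0.3 + 0.2 × 0.2 + 0.1 × 0.19 = 0.273.
- Kappa: (0.85 − 0.273) / (1 − 0.273) = 0.79.
- Numbered A=0, B=1, C=2, D=3: covariance 1.73 − 1.00 × 1.27 = 0.46, variances 1.00 and 1.197, so r = 0.46 / √1.197 = 0.42.
- Numbered A=0, D=1, C=2, B=3: covariance 3.57 − 1.40 × 1.49 = 1.484, variances 1.64 and 1.470, so r = 1.484 / √(1.64 × 1.470) = 0.96.

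The coding is identical and kappa is 0.79 under both numberings, yet r is 0.42 or 0.96. At the extreme, a coder who is always one number higher gives r = 1.0 with 0% agreement.

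**The case against.** **It may be an intraclass correlation.** The word is unqualified in a very short section of a condensed article, and the exact coefficient is often left to a fuller plan. This has some force, but it is not the plain reading, because Sample Size writes out "intraclass correlation coefficient (ICC) of 0.05" when it means one. Only the absolute-agreement form would respond to an offset, and no form suits nominal topic codes. The article has also done more than leave the choice open: it names one statistic for both kinds of data.

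**A correlation does part of the job.** This stands. It reveals random and rank-order disagreement between scores. A reader might infer that the check is worthless for its stated aim, and the text does not support that.

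**Rater offsets need not bias the trial.** This also stands, and it sets the size of the point. A reader might infer that an offset as large as the target effect would enter the results as centre- or state-level bias. Several features of the plan argue against that:

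- Randomization is stratified by state, and the Figure 1 legend says the design is replicated in each state, so a stable state-level offset falls on both groups.
- The primary model has random effects for cluster site and individual, which absorb much of a stable shift between centres.
- The data collector is to be blinded to allocation.
- Participants may complete questionnaires before the visit, which limits the rater's influence on those scores.

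To bias the treatment effect, a rater difference would have to follow intervention status or study period, and the article documents no route for that. It also does not say that different researchers assess outcomes in different states: team members in each state recruit, but data collection is described in terms of a single Research Officer.

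**Conclusion.** The point holds as a minor, quality-control improvement. The plan fixes a statistic that can report good consistency while agreement is poor. For scores, the gap is limited to systematic differences. For coded interviews, the statistic is unsuitable altogether, and this is the stronger half of the point.

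The invariance of the correlation under a constant offset is exact. The ICC values rest on an assumed r of 0.95 or 0.90 and on assumed offsets, and the kappa example rests on an assumed confusion pattern. None of these comes from the document. The offsets show how the statistics behave and do not predict what this trial's raters will do. No claim of bias in the treatment effect follows.

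**What to change.** In Inter-Rater Reliability, replace the single correlation with agreement measures matched to the data type, computed on the same double-rated material:

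- **Coded interview categories:** Cohen's kappa together with percent agreement.
- **Quantitative scores:** the mean difference between the two researchers with limits of agreement, plus an absolute-agreement ICC, naming that form. The mean difference is the essential part, because at an offset the size of the target effect the ICC barely moves.

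The cost is a change of wording and of the statistic computed. No additional ratings, visits or participants are needed.
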